#### Exclusion criteria

Prepregnancy BMI > 30.Low income (unable to afford basic daily needs).Single parents without any kind of family support.Having a child with significant mental/physical disability.Previously diagnosed with other major mental health disorders.Taking prescription medications (other than SSRIs/SNRIs/TCA).Smoking and recreational drug use.Dietary restrictions or allergies to fish oils.Repeated antibiotic use.Women are unable to switch to study brand supplements.Multiparous women with young children (i.e., one or more children less than 4 years of age at the time of delivery).No/low English reading comprehension.

Our inclusion criteria allow for antidepressant/anxiety use. Medication use is an important prognostic factor that can significantly alter mental health outcomes. Hence, the number of patients treated with an antidepressant/anxiolytic needs to be equally distributed among all arms. To achieve this, we will use stratified randomization using two strata (treated vs. untreated) through a computer-generated process using permuted blocks of three and six. The process will be repeated separately for untreated participants.

Preexisting and diagnosed major mental health disorders will be determined at the time of screening using a modified version of the Mini International Neuropsychiatric Interview (MINI). The MINI, conducted by a trained research team member, will allow for confirmation of a history of anxiety/depression and an absence of current anxiety/depression and other major mental health disorders (bipolar, schizophrenia, psychosis, etc.).

### Sample size, recruitment plan, and prestudy screening

While a consensus on an ‘ideal’ sample size for pilot/feasibility studies has not been reached, our proposed number (*N* = 100) meets the recommendation for best practice for the conduct of pilot trials.

This is a single-center study conducted at Sunnybrook Hospital, in Toronto, Canada. Pregnant patients attending obstetrics clinics or The Women’s Mood and Anxiety Clinic at Sunnybrook Hospital will be informed by their attending healthcare provider about the study, and permission to share their contact number with the research team will be requested. Interested patients will be called by a member of the research team and screened for inclusion/exclusion criteria and their ability/status on O3FA and probiotic intake. Patients not willing or unable to take either supplement will receive information about the control arm of the study. Patients willing to take the study supplements will receive information about the interventional arms of the study and the process of randomization. Participants will also be informed that they may receive a placebo instead of probiotics. This design accommodates patient preferences and expectations and emphasizes the goal of an inclusive, pragmatic study design to generate real-world data.

### Randomization and baseline evaluation

All eligible patients interested in participating will be consented to and randomized or assigned to an intervention or control arm based on responses during screening. If eligible for full randomization, this will be completed by the study principal investigator using a computer-generated randomization via random permuted blocks. The study coordinator will only be informed of the status of randomization to the Gutopia arm and will be blinded to the Gutboost and Gutless arms.

Once randomized, the participant will be scheduled for the baseline assessment as soon as possible. If scheduled as a virtual visit, a stool kit will be mailed to the participant or provided at their prenatal visit. There is no predetermined time between the screening and baseline; however, the baseline visit will take place prior to the 35th gestational week (visit 2). The collection of baseline questionnaires will include the following: The Generalized Anxiety Disorder-7 (GAD-7), The Edinburgh Postnatal Depression Scale (EPDS), Single-Item Sleep Quality Scale, Pregnancy Physical Activity Questionnaire Consumer Financial Protection Bureau—Financial Wellbeing (CFPB-FWB), Demographic Questionnaire, and the Dietary Screening Form. Please see the supplementary materials for a breakdown of the versions used and the psychometric properties of each questionnaire. The baseline visit will also include the provision of a stool sample.

There will be a total of six study visits; visit 1 (baseline) and visit 2 will occur during pregnancy, with the remaining four scheduled to take place in the postpartum period (**Figure 1**). All questionnaires completed at baseline, with the exception of the CFBP-FWB, the Demographic Questionnaire, and the Dietary Screening Form, will be completed at all postpartum visits. A postdelivery questionnaire will be completed at visit 3 (~ 4–6 weeks postpartum), and a postpartum questionnaire will be completed at visits 4–6. The sessions will be 45–60 minutes in length.

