## Methods

### Trial design and setting

This is a single-centered, partially randomized placebo-controlled double-blind feasibility trial with three intervention arms (Gutopia, Gutboost, and Gutless) and one active control. In total, 100 pregnant women with a history of depression and/or anxiety/PDA attending Sunnybrook Hospital Clinics in the Greater Toronto Area will be recruited.

Participants in Gutopia will receive a daily dose of both investigational products and dietary counseling on increasing dietary fiber. Participants in Gutboost will receive a daily dose of both investigational supplements, while participants in the Gutless arm will receive fish oil and a placebo. Participants in Gutless and Gutboost will be blinded to the status of the placebo/probiotic they will be receiving. The study member interacting with the patients will also be blinded to the treatment group the participant is assigned to. Participants who fully consent to receiving both investigational products, including placebo, will be fully randomized to one of the intervention arms. Participants not willing or able to take a placebo or probiotics will be assigned (not randomized) to the appropriate group that accommodates their preferences/needs. Participants unable or unwilling to take any of our investigational products will be assigned to the active control arm. Women in the control arm will receive standard care offered to all obstetric patients seen at the hospital.

The study involves six study visits, all of which can be conducted virtually every 3 months from the time of enrollment (**Figure 1**). The last study visit will happen between 9 and 12 months postpartum. Two of the study visits will occur during pregnancy [enrollment (visit 1) and third trimester (visit 2)], with the remaining occurring at 1, 3, 6, and 9 months postpartum. At all study visits, information on diet, mental health, physical activity, and sleep quality will be collected. Additionally, all participants will provide a stool sample at each visit, using our stool collection kits, which will be shipped to or dropped off at our center.

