#### Outcomes measured

As a feasibility study, process evaluation will be our primary outcome. In the first 6 months of the trial, we will monitor the number of patients screened, randomized, and enrolled per month; the average time lapse between screening and enrollment; and the time taken to enroll 15% of our target (i.e., *n* = 15). We will also assess baseline rates of O3FA and probiotics supplementation in this specific cohort prior to randomization. We will identify and document all barriers to meeting the target numbers needed for each study arm and address them appropriately. In patients successfully enrolled, we will also monitor compliance, side effects, and challenges in taking supplements in the intervention groups. We will closely document all issues in adhering to intake instructions and attempt to resolve them on a case-by-case basis (i.e., if forgetfulness is a cause, daily automatic email reminders will be sent to that individual). In Gutopia, attaining a daily fiber target of 35 g/day will be monitored frequently via phone call in the first 6 months or until the patient no longer needs the support. Finally, we will assess retention rates, the proportion of study visits completed, and challenges related to the collection and shipment of stool samples, as well as the completion of questionnaires and dietary recall. All barriers to the timely completion of these tasks will be documented and managed on a case-by-case basis. Strategies to overcome each of these barriers will be proposed in the final write-up of this study.

As part of our secondary aims, we will seek the opportunity to produce preliminary data on the association between maternal microbial response to each intervention and self-reported scores on questionnaires of mental health challenges. This will be for exploratory purposes to identify any signals that will further support the conduct of a larger trial.

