##### Microbial response to diet and supplementation

First, we will assess the microbiome response to each intervention within each group by comparing changes in microbiome composition between baseline (preintervention) and follow-up visits (visits 2–6). The gut profile will be compared between all four arms at each follow-up. The within-group changes from baseline will be compared between groups.

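### Baseline is taken after randomisation and the blinding statements conflict: change-from-baseline comparisons are open to bias, and concealment is at risk though not shown to fail

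*Protocol article*

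**What the plan says.** **Order.** Under *Randomization and baseline evaluation*, eligible women consent and are then randomised, or assigned according to their screening answers. After that, "Once randomized, the participant will be scheduled for the baseline assessment as soon as possible". Visit 1 includes the GAD-7, EPDS, sleep and activity questionnaires, the diet form and a stool sample. One item comes earlier: "We will also assess baseline rates of O3FA and probiotics supplementation in this specific cohort prior to randomization" (*Outcomes measured*).

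**Interval.** "There is no predetermined time between the screening and baseline"; the only bound is that baseline precedes gestational week 35. The MINI, which confirms that there is no current depression or anxiety, is done at screening (text under *Exclusion criteria*).

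**Use of baseline.** *Mental health outcome* compares changes from baseline within and then between groups. *Microbial response to diet and supplementation* plans "comparing changes in microbiome composition between baseline (preintervention) and follow-up visits (visits 2–6") and also compares those changes between groups.

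**Allocation.** For women eligible for full randomisation, "this will be completed by the study principal investigator using a computer-generated randomization via random permuted blocks". The lists are stratified by treated or untreated status, "through a computer-generated process using permuted blocks of three and six".

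**Blinding.** The trial is labelled double-blind. *Trial design and setting* says: "The study member interacting with the patients will also be blinded to the treatment group the participant is assigned to". *Randomization and baseline evaluation* says: "The study coordinator will only be informed of the status of randomization to the Gutopia arm".

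**The concern.** A baseline measured after allocation is protected from the arm only if the arm is hidden. Gutopia includes dietary counselling, so it cannot be hidden from the participant. A woman who knows she has, or has not, been given the fullest package may rate her mood or report her diet differently at visit 1. That shift then enters every change score.

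There is also a gap in the accounting of participants. Under *Criteria for study withdrawal*, lost to follow-up requires that all parts of visit 1 were completed. A randomised woman who leaves before visit 1 falls outside that definition and contributes no baseline score. If such losses differ by arm, the change comparisons no longer describe the randomised groups.

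The blinding and concealment statements matter for the same contrasts. The protocol also intends to continue enrolment into an efficacy trial if feasibility succeeds (end of *Microbiome profiling*), with mental health scores as the primary outcome (*Statistical analysis*), so a weakness here would carry forward.

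**Working it through.** No calculation lies behind the sample size. The arms add up (75 + 25 = 100), and nothing below depends on power.

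**1. Which analyses use the post-allocation baseline?**

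| Analysis | Section | Uses baseline value? |
|---|---|---|
| Recruitment, compliance, retention, visit completion (primary) | Outcomes measured | No |
| Group means and medians of EPDS/GAD-7 | Mental health outcome | No |
| Change from baseline, within and between groups | Mental health outcome | Yes |
| Microbiome change, within and between groups | Microbial response | Yes |
| Gut profile across arms at each follow-up | Microbial response | No |
| ANCOVA on EPDS/GAD-7 (covariates: pharmacotherapy, exercise, psychotherapy) | Statistical analysis | Not as listed |
| Repeated-measures ANOVA within group | Statistical analysis | Yes |

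**2. Size of the bias.** Let *d* be the shift in mean baseline EPDS in Gutopia caused by knowing the arm, with follow-up scores unaffected.
- Observed change = follow-up − (true baseline + *d*).
- The Gutopia-minus-comparator change contrast therefore moves by −*d*: 0 if *d* = 0, and 1 point if *d* = 1. The documents give no value for *d*; 1 point is an illustration.
- Randomised Gutboost versus Gutless: women in both arms can know only that they are not in Gutopia, so any shift is common and *d* − *d* = 0.

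**3. Screening-to-baseline interval.** Enrolment opens at week 12 and baseline must precede week 35: 35 − 12 = 23 weeks at most, taking screening as no earlier than week 12. No repeat of the MINI is stated.

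**4. Blinding statements side by side.**
- *Trial design and setting* states that the staff member interacting with patients is blinded to treatment group.
- *Randomization and baseline evaluation* tells the coordinator who is in Gutopia.
- *The intervention* gives only Gutopia a dietary intervention, with weekly follow-up by a trained team member. That person interacts with patients and must know the arm.
- Participant blinding is claimed only for Gutboost and Gutless, and only for probiotic versus placebo.

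The first statement cannot hold for all patient-facing staff, and the double-blind label cannot cover all four arms.

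**5. How predictable is the next allocation?** Simulation of 2,000 sequences, of 75 women and of 37 (about one stratum). Assumptions: 1:1:1 ratio, block sizes 3 and 6 equally likely, and an observer who knows these sizes and sees every earlier allocation in the stratum.

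| Observer sees | Next allocation certain | Best guess correct | Without information |
|---|---|---|---|
| Gutopia or not | about 10% (2% Gutopia, 8% not) | about 75% | 66.7% (always guess not Gutopia) |
| All three arms | 8–9% | 57–58% | 33.3% |

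In a separate simulation of 400,000 blocks, the chance that the next woman gets Gutopia was 18% just after a Gutopia allocation, 50% after two non-Gutopia and 59% after three, against 33% if unpredictable. These are selected states, so the table is the fairer summary. Seeing Gutopia status alone says nothing about Gutboost versus Gutless.

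**The case against.** The strongest reply is that the baseline is described as preintervention, so no product effect can enter it. In Gutopia the dietitian builds the plan from the baseline food data, so counselling follows the diet form. Baseline is to follow randomisation promptly, the document does not say when women learn their arm, and the trial's primary outcomes are process measures. All of this stands. It confines the problem to expectation and selective loss in the change comparisons that involve Gutopia.

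Four stronger readings are tempting, and the documents do not support them:
- **Concealment has failed.** Nothing says that the principal investigator or the coordinator screens or enrols; screening is by an unspecified member of the research team. Custody of the list may be covered in the full protocol. The gain in guessing Gutopia is 75% − 67%, about 8 percentage points. This is a risk only.
- **Every analysis is biased.** The table in the working shows otherwise.
- **Baseline may come 23 weeks after allocation.** The 23 weeks is the worst case from screening. From randomisation the instruction is as soon as possible.
- **Re-ordering would protect all arms.** Control women enter that arm because they cannot or will not take the products, and preference-assigned women are placed to suit a stated preference. They can know their arm before visit 1 whatever the order.

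It can also be said that the coordinator need not be the patient-facing member, which would remove that contradiction. The Gutopia-only follow-ups still contradict the statement as written.

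**Conclusion.** The point holds in a limited form. For randomised women, baseline EPDS, GAD-7, diet and stool are collected after allocation, when those in Gutopia may already know their arm, and women lost before visit 1 have no baseline. The change-from-baseline comparisons in *Mental health outcome* and *Microbial response* that involve Gutopia are exposed. The bias equals whatever shift knowledge of the arm produces, and the documents do not allow that shift to be estimated. The primary feasibility outcomes, the ANCOVA as listed and the blinding of randomised Gutboost versus Gutless are not affected by this route.

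Three further statements hold. The screening-to-baseline interval is unrestricted, at worst about 23 weeks, although stability is confirmed only at screening. The double-blind label and the statement on patient-facing staff conflict with other sections. Randomisation by the principal investigator with published short blocks puts concealment at risk, to the modest degree calculated under the stated assumptions, but no failure is demonstrated.

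**What to change.** - For women eligible for randomisation, complete the visit 1 questionnaires and stool sample before the allocation is released. Prior supplement use is already to be assessed before randomisation, so some pre-allocation data collection is planned.
- Have the allocation released by a system, or by a person independent of enrolment and assessment, and do not disclose block sizes to recruiting staff.
- Set a screening-to-baseline window.
- Restrict the double-blind label to randomised Gutboost versus Gutless. Describe the Gutopia, control and preference-assigned contrasts as open.
- Reconcile the blinding statements in *Trial design and setting*, *Randomization and baseline evaluation* and *The intervention*.
- State as a limitation that control and preference-assigned women can know their arm at baseline, which re-ordering does not change.

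The cost is a change in the order of steps, set-up of the allocation release and some rewording. Product start has to wait for the baseline forms and stool sample.

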### Participant eligibility

#### Inclusion criteria

A person aged 18–43 years old.At 12–35 weeks of gestation at the time of enrolment.Uniparous pregnancy.A nonsmoker, alcohol, or recreational drug user.Financially stable.In a married or common-law relationship.Clinical diagnosis of lifetime depression/anxiety or PDA (stable since the conception of the current pregnancy).No other significant comorbidities.Ability to read in English and provide informed consent.

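### The timing rules for enrolment, baseline and visit 2 conflict, and visits every 3 months from enrolment cannot coexist with the delivery-anchored schedule

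*Protocol article*

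**What the plan says.** Four timing statements in the Protocol article bear on the same visits.

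- **Inclusion criteria:** women are eligible "At 12–35 weeks of gestation at the time of enrolment".
- **Randomization and baseline evaluation:** "the baseline visit will take place prior to the 35th gestational week (visit 2" (the bracket closes there). The same section says "visit 1 (baseline) and visit 2 will occur during pregnancy, with the remaining four scheduled to take place in the postpartum period", and places visit 3 at about 4 to 6 weeks after delivery.
- **Trial design and setting, visit spacing:** there are six visits, "all of which can be conducted virtually every 3 months from the time of enrollment". The abstract repeats this.
- **Trial design and setting, visit events:** the pregnancy visits are "enrollment (visit 1) and third trimester (visit 2)], with the remaining occurring at 1, 3, 6, and 9 months postpartum". The section adds: "The last study visit will happen between 9 and 12 months postpartum".

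Enrolment and visit 1 are treated as the same event. Outcomes measured lists the proportion of study visits completed among the primary process outcomes. Microbiome profiling expects six stool samples per woman, and Microbial response to diet and supplementation compares baseline with visits 2 to 6.

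**The concern.** The visit calendar is given by two different clocks, one starting at enrolment and one tied to the third trimester and to delivery. The upper limit for enrolment also does not fit the deadline for baseline. Staff cannot follow all the statements for every eligible woman.

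Two things are at stake. First, visit completion is part of the primary outcome. Under Criteria for study withdrawal, a visit not rescheduled within 4 weeks is marked as lost to follow-up. A visit 2 that delivery has pre-empted could then be counted as poor feasibility when the schedule caused it, and that woman could not give six stool samples. Second, visit 2 is the only follow-up during pregnancy. If its distance from baseline varies widely, the change in EPDS, GAD-7 or stool profile at visit 2 mixes very different lengths of exposure. The article intends to continue enrolment into an efficacy trial if this one succeeds, so the ambiguity would carry forward.

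**Working it through.** **Inputs from the article:** enrolment at weeks 12 to 35; baseline before the 35th week; visits 1 and 2 in pregnancy, with visit 2 in the third trimester; visits 3 to 6 at 1, 3, 6 and 9 months postpartum; last visit at 9 to 12 months postpartum; alternatively, six visits 3 months apart from enrolment.

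**Assumptions not in the article:** the third trimester starts at week 28 (range 27 to 29); delivery is at week 40 (range 37 to 42). One month = 365.25/12/7 = 4.348 weeks; three months = 13.04 weeks.

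**1. Eligibility against baseline.** A woman in week 35 meets the inclusion criterion but has passed the baseline deadline. The width of the conflict depends on how weeks are counted. If eligibility runs through 35+6 and the deadline means before 35+0, the gap is one week. If the 35th week is counted as an ordinal, starting at 34+0, it is about two weeks. If eligibility stops at 35+0 and the deadline is also 35+0, it shrinks to a single day.

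**2. Postpartum spacing.** From 1 to 3 months postpartum is 3 − 1 = 2 months. The 3-month rule therefore fails for every participant, whenever she enrolled.

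**3. Visit 2 under the 3-month rule, and its gap from baseline if it is at week 35.**

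| Enrolment week | Visit 2 at enrolment + 13.04 (week) | Gap to week 35 (weeks) |
|---|---|---|
| 12 | 25.0 | 23 |
| 15 | 28.0 | 20 |
| 22 | 35.0 | 13 |
| 27 | 40.0 | 8 |
| 30 | 43.0 | 5 |
| 34 | 47.0 | 1 |
| 35 | 48.0 | 0 |

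The latest enrolment that keeps a 3-month visit 2 in pregnancy is 40 − 13.04 = week 27.0 (37 − 13.04 = 24.0; 42 − 13.04 = 29.0). The earliest that puts it in the third trimester is 28 − 13.04 = week 15.0 (range 14 to 16). The two rules agree on visit 2 only for enrolment at about weeks 15 to 27.

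**4. Last visit under the 3-month rule.** Visit 6 falls 5 × 13.04 = 65.2 weeks after enrolment. With delivery at week 40, that is (12 + 65.22 − 40)/4.348 = 8.6 months postpartum for enrolment at week 12, and (35 + 65.22 − 40)/4.348 = about 13.9 months for week 35. Both lie outside the stated 9 to 12 months.

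**5. Interval from baseline to visit 2.** If visit 2 is fixed at week 35, the interval is 35 minus the enrolment week: 23 weeks at the lower limit, 1 week for enrolment at week 34, and under 1 week for a baseline just before a deadline of 35+0. If visit 2 may fall anywhere in the third trimester, a woman enrolled at week 34 has up to 40 − 34 = 6 weeks before delivery (3 to 8), and one enrolled at week 35 up to 5 weeks (2 to 7).

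**6. Illustrative scale.** The article gives no distribution of enrolment week. If it were uniform over the 35 − 12 = 23 weeks, a 3-month visit 2 would fall after delivery for (35 − 26.96)/23 = 35% (26% to 48% for delivery at 42 to 37 weeks), and before week 28 for (14.96 − 12)/23 = 13%. These shares apply only if the 3-month rule governs.

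**The case against.** The strongest reply is that the 3-month phrase is a loose summary. The event-anchored schedule follows it directly, and a later section repeats the split into two pregnancy and four postpartum visits, so the specific schedule plausibly governs. That is a fair reading and it removes the postpartum visit 2. It leaves the conflict between eligibility and baseline, and a sentence that is wrong for every participant and appears twice.

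A reader might infer that late enrollees have no usable visit 2. The documents do not support that. It needs visit 2 to be fixed at week 35, or the 3-month rule to override the rest. Trial design and setting says only third trimester, and the visit 2 label on the 35th week is ambiguous: it may date visit 2 or be a slip for visit 1. Most late enrollees could still be seen before delivery, after a short and uneven interval. A baseline that itself falls in the third trimester breaks no stated rule.

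It can also be said that visit windows and minimum intervals belong in the full protocol, and that the visit diagram is not shown. That is accepted. The point rests on statements that disagree, not on a missing window.

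Finally, the mental-health and microbiome comparisons are exploratory here, and the ANCOVA plan is conditional on a larger trial. Chance imbalance aside, uneven intervals do not bias comparisons among randomized arms. That protection does not extend to the control arm or to women assigned by preference. The article also promises to document barriers to timely completion, so a schedule-caused miss need not go unnoticed, but it does not say how such a miss enters the completion rate.

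**Conclusion.** The timing statements conflict and should be reconciled. Two contradictions need no modelling: a woman enrolled in week 35 has no permitted baseline (a gap of a day to about two weeks, depending on how weeks are counted), and 3-monthly visits cannot match visits at 1 and 3 months postpartum. A third depends on gestation at delivery: enrolment after about week 27 (24 to 29) puts a 3-month visit 2 after delivery, although it is required in pregnancy.

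Visit 2 is not a comparable exposure point if it is at week 35, because the interval from baseline then runs from about 23 weeks to under 1 week. If any third-trimester date is allowed, the problem is a short, uneven interval for late enrollees rather than a lost visit. No sample size or power figure is affected, and the uniform-enrolment shares show scale only. This is a should-fix, not a flaw that undermines the design.

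**What to change.** - Delete the 3-monthly spacing from Trial design and setting and from the abstract. Keep one anchor per visit: visit 1 at enrolment, visit 2 in a stated third-trimester window chosen by the sponsor, visits 3 to 6 by delivery date.
- Make the latest enrolment week in the Inclusion criteria agree with the baseline deadline, and say how gestational weeks are counted. Correct or explain the visit 2 label attached to the 35th week.
- In the visit and stool completion rates, show visits 2 pre-empted by delivery as a separate category from other missed visits. Do not drop them, because whether late enrolment is workable is itself a feasibility result.
- Report visit 2 EPDS, GAD-7 and stool results by weeks since baseline or first dose.

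The cost is protocol wording, a visit-window setting in the database, a little more reporting, and possibly an enrolment cut-off one to two weeks earlier.
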